#### Other Outcomes

Table 5 shows other outcome measures.

**Table 5. T5:** Other outcome measures.

Outcome category	Outcome number	Outcome	Description	Measurement time points
Messages recall
	38	Free recall (yes or no)	Participant is asked if they saw any prevention pop-up messages during their gambling session in the laboratory. This is a yes or no question.	Assessed at the end of the gambling session
	39	Free recall (number)	If the participant declared that they saw prevention pop-up messages during their gambling session in the laboratory, they are asked how many there were. The same message presented twice counts as “2”.	Assessed at the end of the gambling session
	40	Free recall (content)	If the participant declared they saw prevention pop-up messages during their gambling session in the laboratory, they are asked to freely describe them (ie, content, graphical appearance, etc).	Assessed at the end of the gambling session
	41	Cued recall (yes or no)	The participant is presented with a list of prevention pop-up messages that could have been shown during the study. For each of them, they are asked to identify if they saw it or not.	Assessed at the end of the gambling session
	42	Cued recall (number)	If the participant declared that they saw prevention pop-up messages during their gambling session in the laboratory, they are asked how many there were. The same message presented twice counts as “2”. This is different from outcome 39 because the participant might recognize a message they had forgotten about or a message they saw but did not consider it a “prevention message.”	Assessed at the end of the gambling session

### Statistical Methods

Sociodemographic variables, past 12 months of gambling-related variables, and PGSI category will be presented in a table with appropriate central tendency estimates. This table will be divided by assignation group.

A total of 3 statistical models will be used to analyze the outcomes presented in Tables3  4. All these models will control for the time-varying covariate “gains-losses differential” (ie, remaining balance on the EGM at measured time point minus money inserted in the EGM from the start of the study). All models will also test the moderation effect of the following variables: gender (men or women), age (continuous), education (5 categories), and PGSI category (nonproblem, low risk, and moderate risk). Holm-Bonferroni correction [85] will be used to counteract family-wise error rate due to multiple comparisons in each model for each statistically significant categorical variable (ie, time for repeated measures ANCOVAs; moderators with ≥3 categories).

The first model uses ANCOVAs to examine the differences between the two groups at the end of the gambling session on outcome variables 1, 3, 4, 6‐9, 14, 16, 17, and 19, separately.

The second model uses repeated measures ANCOVAs to examine the differences between the two groups at specific time points during the experiment corresponding to the presentation of the prevention pop-up messages in the experimental group. This model is computed on outcome variables 1 and 10‐13, separately.

The third model uses repeated measures ANCOVAs to examine the differences between self-reported measures (past 12 months) and the observed behaviors during the experiment. This model is computed on outcome variables 2, 5, 15, and 18, separately.

Secondary and other outcomes will be documented but will not be statistically compared. Descriptive estimates will be provided for each quantitative variable. Open-ended questions will be analyzed in a manner inspired by the thematic analysis method (see Textbox 3) [86].

Textbox 3.The 5 steps in analysis of open-ended questions.Interviewer’s notes are regrouped in a Microsoft Word document.Raw data is carefully read, both by main author and another member of the research team, to extract categories of similar content.Categories are refined by both coders.Raw data is independently categorized in appropriate categories by both coders.Intercoder agreement is calculated on all categorizations to ensure reliability.

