### Sample Size Considerations

Using G*Power, we estimated the required sample size for an α level of 5% and ß level of 80% for a 2-tailed *t* test for a range of effect sizes (see Table 1). This was done both for testing differences in outcomes between 2 independent groups and for repeated measures.

**Table 1. T1:** Required sample size for a range of effect sizes.

Effect size (*g*)^a^	Per group, n (%)	Total, N
0.2	394 (50)	788
0.3	176 (50)	352
0.4	100 (50)	200
0.5	64 (50)	128
0.6	45 (50)	90
0.7	34 (50)	68
0.8	26 (50)	52
0.9	16 (50)	32

a Calculated for an α level of 5% and ß level of 80% for a 2-tailed *t* test.

A recent meta-analysis by Bjørseth et al [18] on the effects of RG pop-up messages on gambling behaviors and cognitions reports effect sizes respectively of *g*=0.62 (95% CI 0.36-0.87 and *g* 0.58 (95% CI 0.33‐0.83) when adjusting for publication bias. Based on those values, the total sample size would be between 86 and 96. Note that sample size requirements for 1-way analysis of covariances (ANCOVAs) and repeated measures analyses would be equal to or smaller. Considering the potential difficulty in recruiting participants accepting to play with their own money, we aimed at a sample size of 80. Therefore, we can expect a power range from 72.34% to 77.66% with effect sizes comparable to what is reported by Bjørseth et al [18].

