### Outcome Assessments

Table 3 shows the primary outcome measures.

**Table 3. T3:** Primary outcome measures.

Outcome category	Outcome number	Outcome	Description	Measurement time points
Gambling behavior: Money				
	1	Money betted (physical)	Cumulative amount of money physically inserted in the EGM^a^ during the gambling session.	Assessed at the following time points from start of gambling session in the laboratory: [0] T+00:00:00, [1] T+00:10:00, [2] T+00:40:00, [3] T+01:10:00, [4] T+01:40:00, [5] end of gambling session (max T+02:00:00)
	2	Change in money betted (physical)	Change between self-reported measures (past 12 months) and observed data in the laboratory.	Past 12 months; end of the gambling session
Gambling behavior: Time				
	3	Gambling session’s total duration	Time elapsed between the first time the participant puts money in the EGM (T+00:00:00) to the end of the gambling session. Session’s duration is left for the participant to decide. While the participant is told they can play for as long as they like, there is a 2 h limit on the session duration. This limit is hidden from the participant. Session’s duration includes any breaks taken from gambling on the EGM.	Assessed at the end of the gambling session.
	4	Total time effectively spent gambling	Time elapsed between the first time the participant puts money in the EGM (T+00:00:00) to the end of the gambling session, minus breaks taken from gambling on the EGM.	Assessed at the end of the gambling session.
	5	Change in total time effectively spent gambling	Change between self-reported measure (past 12 months) and observed data in the laboratory	Past 12 months; end of the gambling session.
Gambling behavior: Breaks				
	6	Number of breaks taken	Number of breaks taken from gambling on the EGM during the gambling session.	Assessed at the end of the gambling session.
	7	Mean breaks’ duration	Average duration of breaks taken from gambling on the EGM over the gambling session’s total duration.	Assessed at the end of the gambling session.
	8	Total breaks duration	Sum of breaks’ duration taken from gambling on the EGM over the gambling session’s total duration.	Assessed at the end of the gambling session.
	9	Mean time elapsed between breaks	Average time separating any two breaks taken from gambling on the EGM over the gambling session’s total duration.	Assessed at the end of the gambling session.
Gambling behavior: Risk taking				

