	16	Perceived behavioral effectiveness of prevention pop-up messages	Participant’s perceived effectiveness of prevention pop-up messages on modifying their gambling behavior during the gambling session. Evaluated with two 7-point Likert scales about the perceived effects of the prevention pop-up messages on money betted and time spent during the gambling session (1=“lowered gambling behavior a lot” to 7=“heightened gambling behavior a lot”).	Assessed at the end of the gambling session.
Emotions				
	17	General level of fun while gambling on EGMs	Participant’s general enjoyment of gambling on EGMs over the gambling session’s total duration. Evaluated with a 7-point Likert scale (1=“I hated it” to 7=“I loved it”).	Assessed at the end of the gambling session.
	18	Change in general level of fun while gambling on EGMs	Change between self-reported measures (past 12 months) and observed data in the laboratory.	Past 12 months; end of the gambling session.
	19	Psychological reactance to prevention pop-up messages (between group)	Evaluated based on Dillard and Shen [84] method: (1) Induction check (4 items, 7-point Likert scale, 1=“Strongly disagree, 7=“Strongly agree”); (2) Anger (4 items, 7-point Likert scale, 1=“Strongly disagree, 7=“Strongly agree”); (3) Cognitive response (count of negative thoughts in relation to the pop-up messages); and (4) Attitude (7 word pairs, 7-point semantic differential scale).	Assessed at the end of the gambling session.

a EGM: electronic gambling machine.

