## Discussion

### Principal Findings

The main objective of this study is to test the potential of pop-up messages as a prevention measure in a gambling setting. Effects of messages are measured on behaviors, cognitions, and emotions. The optimal benefit from the messages would be observing a reduction in money bet during the gambling session. However, other behavioral effects, like reduction in gambling intensity or session lengths, are considered indirectly beneficial because they foster conditions for further preventive actions. For example, all things being equal, a reduction in gambling intensity reduces the amount of money lost per unit of time. This, in turn, gives more time to the person gambling to think about their behavior and potentially stop their session with some money left. The improved realism of our research design heightens the confidence that the effects observed in our study can successfully be transposed to a real gambling setting.

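### Nineteen co-equal primary outcomes and a Holm correction confined to comparisons inside each model leave the group effect uncontrolled across 15 outcomes, while the stated power fits one 5% test

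*Protocol article*

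**What the plan says.** Outcome Assessments states that "Table 3 shows the primary outcome measures". The table runs from outcome 1 (cash inserted in the machine) to outcome 19, "Psychological reactance to prevention pop-up messages (between group"), with no order of importance.

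Statistical Methods assigns these outcomes to three models, each outcome analysed on its own:
- Model 1, ANCOVA between groups at the end of the session: outcomes 1, 3, 4, 6-9, 14, 16, 17 and 19.
- Model 2, repeated measures ANCOVA between groups at the message time points: outcomes 1 and 10-13.
- Model 3, repeated measures ANCOVA of the past 12 months' self-report against laboratory behaviour: outcomes 2, 5, 15 and 18.

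Every model adjusts for the gains-losses differential and tests four moderators. On multiplicity: "Holm-Bonferroni correction [85] will be used to counteract family-wise error rate due to multiple comparisons in each model for each statistically significant categorical variable". The sentence then limits those variables to time and to moderators with at least three categories.

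The sample size table is "Calculated for an α level of 5% and ß level of 80% for a 2-tailed" t test, and with 80 participants the section concludes: "Therefore, we can expect a power range from 72.34% to 77.66% with effect sizes comparable to what is reported by" the cited meta-analysis. In the Discussion, Principal Findings says: "The optimal benefit from the messages would be observing a reduction in money bet during the gambling session".

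**The concern.** Group has two levels and is not among the variables that Holm covers, and the correction stops at the edge of each model. Each between-group primary outcome therefore gets its own unadjusted test of the messages. Principal Findings names money bet as the best outcome but also counts lower intensity and shorter sessions as indirect benefits, so several different significant results could support a claim that the messages work. With no outcome named in advance, a positive finding on the first objective cannot be read as confirmatory. The power statement also describes a trial with one test, which is not the trial that the analysis section sets out.

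**Working it through.** **Inputs.** Two-sided 5% level, 40 per arm (80 at 1:1), g = 0.62 for behaviours and 0.58 for cognitions (Sample Size Considerations); outcome lists (Statistical Methods). The 5% level appears only in the sample size section. Using it as the test level is an assumption.

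**1. The plan's own power.** A two-sided, two-sample t test at 5% with 40 per arm (noncentral t) gives 72.6% at g = 0.58 and 78.2% at g = 0.62, against the stated 72.34% and 77.66%. For 80% power it needs 84 to 96 in total, against the stated 86 to 96. The stated power is reproduced closely, for one test.

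**2. Count of between-group analyses.**
- Model 1: 1, 3, 4, 6, 7, 8, 9, 14, 16, 17, 19 = 11.
- Model 2: 1, 10, 11, 12, 13 = 5.
- Sum 11 + 5 = 16 analyses. Outcome 1 is in both, so 15 distinct outcomes.
- Model 3: 2, 5, 15, 18 = 4, not described as arm contrasts. 15 + 4 = 19.

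Outcome 16 is "Evaluated with two 7-point Likert scales about the perceived effects of the prevention pop-up messages on money betted and time spent", and outcome 19 has four components. Scored separately, these would raise the count.

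**3. Chance of at least one false positive group effect, all nulls true, independent tests:** 1 - 0.95^k.
- k = 15: 1 - 0.95^15 = 53.7%.
- k = 16: 1 - 0.95^16 = 56.0%.
- For comparison, all 19 outcomes: 1 - 0.95^19 = 62.3%.

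**4. Allowing for correlation.** The article gives none, so a common correlation r between normal test statistics is assumed. The chance is 1 - ∫ φ(z) [Φ((1.96 - √r z)/√(1-r)) - Φ((-1.96 - √r z)/√(1-r))]^k dz.

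| Assumed r | 16 tests | 19 tests |
|---|---|---|
| 0.3 | 48% | 52% |
| 0.5 | 37% | 41% |
| 0.7 | 26% | 28% |
| 0.9 | 15% | 15% |

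**5. Scope of the correction.** Holm as written compares time points, and categories of education or PGSI, within one model. None of the 16 group effects enters it.

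**The case against.** The size is easy to overstate, and four stronger readings do not stand.

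- A reader might infer a false positive chance of about 60%. That value needs 19 independent group tests. Model 3 is described as self-report against laboratory behaviour, which matches feasibility question 5.5, a secondary objective. The outcomes also overlap by construction: outcome 4 is outcome 3 less breaks, and outcomes 11 and 12 are outcomes 10 and 1 per minute.
- A reader might infer that any of the 19 outcomes could carry the claim of benefit. The Discussion treats reactance as a possible explanation of negative results and hopes for no loss of enjoyment. On the 12 behavioural analyses alone (7 in Model 1, 5 in Model 2), counting only errors that favour the messages, independence gives 1 - 0.975^12 = 26%. That is smaller, but still about five times 5%.
- A reader might infer that the article claims control across outcomes and fails to deliver it. The sentence claims control only within each model.
- A reader might pool the moderator tests into the primary error rate. The article lists moderation as a secondary objective.

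An SAP that is not shown may add detail. The article nevertheless fixes two things itself: the primary label on 19 outcomes and the scope of the correction. The defect therefore stands at a smaller size.

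**Conclusion.** The point holds. Nineteen outcomes share primary status, 15 of them receive 16 between-group analyses, and no rule controls the group effect across them. The false positive chance is up to about 54-56% under independence. With correlation it is lower but well above 5% throughout the range examined, about 15% even at 0.9. These figures assume that the sample size section's two-sided 5% is the test level, that outcomes 16 and 19 count once each, and that Model 3 contributes no arm contrast. The stated power of 72-78% is right for one test and does not describe the set. For a behavioural primary, only the value at g = 0.62, about 78%, applies.

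**What to change.** Make a dated amendment, declared as made before any arm-level analysis. Timing matters because recruitment has ended and the research team is not masked to assignment; the article reports no results yet.

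- **Primary outcome.** Name one outcome and one model at two-sided 5%. Outcome 1 at the end of the session is the natural candidate given Principal Findings. The sponsor should first confirm whether money bet there means cash inserted (outcome 1) or all money wagered, including re-bet winnings (the basis of outcome 13).
- **Primary model.** Take the group effect from a model without interactions and without the gains-losses differential. That covariate is the remaining balance minus money inserted, so it contains outcome 1, and it is measured after randomisation.
- **Power.** Quote about 78% (g = 0.62) for a behavioural primary.
- **Other between-group outcomes.** Make them secondary, with Holm across group effects within the behaviour, cognition and emotion families, or report estimates with 95% confidence intervals and no significance claims.
- **Moderators.** Treat these tests as exploratory.

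The text change is small: relabelling Table 3 and rewriting one paragraph of Statistical Methods. The real cost is that secondary findings carry less weight and that the published primary outcomes change after recruitment closed, which the report must disclose and justify.

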#### Presentation of the Study and Verbal Consent

After satisfying the screening criteria, participants are presented with the details of the study. Participants are recruited for a single gambling session in a bar replica equipped with EGMs. Recruitment is done under the false pretense of evaluating the realism of a gambling session in a laboratory replicating a bar. The main points communicated to the participants during the presentation of the study are:

Gambling is done with your own money. You must bring the amount they wish to gamble the day of the experiment.Winnings are paid up to CA $500 more than the total amount inserted in the EGM over the course of the gambling session (eg, if you insert CA $60 in the EGM during your session, you could be paid up to CA $560). In turn, losses are real. There is no baseline compensation for participating in the study. The only compensation for participation is the potential winnings made while gambling. Overall, it is possible to end the study with less money than at the beginning, even to lose it all.The EGMs used in this study are of the same model currently in operation in Quebec, Canada. Their payout rate is the same (92%).You are free to gamble as much and for as long as you like.You are allowed to take breaks.Snacks and nonalcoholic beverages can be purchased with real money during the study via cash or electronic transactions.

Participants who give their verbal consent proceed with the intake interview.

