**Figure 6. F6:**
[figure not shown]
Observation post.

The session ends when one of the two following conditions is met: (1) the participant expresses, without ambiguity, that they wish to end the experiment, and (2) T+02:00:00 is reached. The procedure may slightly vary depending on how the gambling session ends. Under normal circumstances, the participants end their session by themselves, before reaching the T+02:00:00 time limit. In this scenario, the procedure continues normally, as described in the postexperimentation phase section. Alternative scenarios are:

Alternative scenario 1: The participant reaches the T+02:00:00 time limit and continues to play. The member of the research team, playing the role of bartender, interrupts the participants and suggests taking a pause to answer some questions. If the participant agrees, the procedure continues normally, as described in the postexperimentation phase section. Unbeknownst to them, they will not be allowed to resume gambling after said questions.Alternative scenario 2: Same as “Alternative scenario 1,” but the participant refuses and insists on continuing to play, and debriefing is done on the spot to end the play session. All questionnaires presented in the postexperimentation phase section are done, but contrary to the normal scenario, evaluation of participants’ perception of the realism of the bar replica and of the gambling session is done after debriefing.Alternative scenario 3: The participants try to hastily quit the laboratory before we get a chance to debrief them (eg, because they are angry about losing a lot of money and do not wish to participate any longer). In this case, debriefing is done early to prevent them from quitting without receiving all the information to make an informed decision about their participation. All questionnaires presented in the postexperimentation phase section are done, but contrary to the normal scenario, evaluation of participants’ perception of the realism of the bar replica and of the gambling session is done after debriefing.

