#### Prevention Pop-Up Messages

Messages are shown full screen on the EGM’s play screen on a fixed presentation schedule from the moment the participant inserts money for the first time in the EGM (ie, T+00:00:00). The first message is shown at T+00:10:00. Messages block the play screen for 15 seconds before automatically closing. This presentation frequency is thought to be a good compromise between a very high and potentially annoying frequency (eg, [21,48]) and a very low frequency where only a few participants are exposed (eg, [23]). The first message is presented sooner than the others so that every participant has a decent chance to see at least one. The subsequent presentation schedule is modeled on Schrans et al [50]. While it would have been ideal that messages stay on until participants close them, this was not possible due to hardware limitations on the EGMs’ part. The 15-second presentation duration was chosen based on the mean reading speed of a typical francophone adult [76], so participants have enough time to read the messages.

Up to 4 different messages are presented during the gambling session. Order is determined by sortition without replacement. Variations were introduced to counter the possible habituation effect [19,64]. All messages follow the same template (see Textbox 2 and Figure 9 for an example and see Multimedia Appendix 3 for every message used in the study).

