	10	Number of bets placed	Number of bets placed on the EGM during the gambling session.	Assessed at the following time points from start of the gambling session in the laboratory: [0] T+00:00:00, [1] T+00:10:00, [2] T+00:40:00, [3] T+01:10:00, [4] T+01:40:00, and [5] at the end of the gambling session (max T+02:00:00).
	11	Gambling speed	Number of bets placed on the EGM during the gambling session over a given amount of time (ie, bets/min).	Assessed at the following time points from start of the gambling session in the laboratory: [0] T+00:00:00, [1] T+00:10:00, [2] T+00:40:00, [3] T+01:10:00, [4] T+01:40:00, and [5] at the end of the gambling session (max T+02:00:00).
	12	Gambling intensity (physical)	Money physically inserted in the EGM during the gambling session over a given amount of time (ie, $/min).	Assessed at the following time points from the start of the gambling session in the laboratory: [0] T+00:00:00, [1] T+00:10:00, [2] T+00:40:00, [3] T+01:10:00, [4] T+01:40:00, and [5] end of the gambling session (max T+02:00:00).
	13	Gambling intensity (all)	Money betted on the EGM during the gambling session over a given amount of time (ie, $/min). This is money used to “buy rounds on the EGM,” whether it's money physically inserted in the EGM or money won while gambling and betted again.	Assessed at the following time points from the start of the gambling session in the laboratory: [0] T+00:00:00, [1] T+00:10:00, [2] T+00:40:00, [3] T+01:10:00, [4] T+01:40:00, [5] end of the gambling session (max T+02:00:00).
Cognitions				
	14	Perceived self-control while gambling on EGMs	Participant’s perceived ability to control their gambling behavior (eg, sticking to their predetermined limits) over the gambling session’s total duration. Evaluated with a 7-point Likert scale (1 = “I never had control” to 7 = “I always had control”).	Assessed at the end of the gambling session.
	15	Change in perceived self-control while gambling on EGMs	Change between self-reported measure (past 12 months) and observed data in the laboratory	Past 12 months; end of the gambling session.

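### Model 2 compares the arms at fixed clock times although participants choose when to stop, so late contrasts rest on a subset selected after randomisation or, for the rates (outcomes 11–13), restate stopping time or total bets

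*Protocol article*

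**What the plan says.** Statistical Methods defines the analysis: "The second model uses repeated measures ANCOVAs to examine the differences between the two groups at specific time points during the experiment". The time points are said to correspond to the message presentations. The section continues "This model is computed on outcome variables 1 and" 10–13, each analysed separately. These outcomes are cumulative money inserted (1), number of bets (10), bets per minute (11), money inserted per minute (12) and money bet per minute (13). Outcomes 10–13 appear in no other model.

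Table 3 gives the measurement times for these outcomes as T+0 and then "1] T+00:10:00, [2] T+00:40:00, [3] T+01:10:00, [4] T+01:40:00, [5] end of gambling session (max T+02:00:00". The speed outcome is defined as "Number of bets placed on the EGM during the gambling session over a given amount of time (ie, bets/min".

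The participant decides how long to play. The briefing (Presentation of the Study and Verbal Consent) tells them: "You are free to gamble as much and for as long as you like". Table 3 adds that "there is a 2 h limit on the session duration", which is hidden from them. Gambling Session in the Laboratory describes the expected course: "Under normal circumstances, the participants end their session by themselves, before reaching the T+02:00:00 time limit". The design also allows for very early stopping (Prevention Pop-Up Messages): "The first message is presented sooner than the others so that every participant has a decent chance to see at least one".

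Session duration is primary outcome 3, and Principal Findings counts shorter sessions as an indirect benefit of the messages.

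**The concern.** Whether a participant contributes play at T+40, T+70 or T+100 is decided after randomisation, by a behaviour that the messages are meant to change. A contrast among people still playing at T+100 is not protected by randomisation. If messages lead lighter gamblers to leave sooner, those who remain in the experimental arm are the heavier ones. Messages that worked could then look useless or harmful for speed and intensity.

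The rates carry most of the risk. After a participant stops there is no play to divide by, and the usual ways round this either select participants or change the question. Model 2 is the only test of three primary rate outcomes (11–13) and of the number of bets (10).

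**Working it through.** **1. The plan's own figure.** The article states power of 72.34% to 77.66% for 80 participants and g = 0.58 to 0.62. A two-sided two-sample t test at 5% with 40 per arm (noncentral t) gives 72.6% and 78.2%, which agrees closely. That figure assumes all 80 contribute at a single time point.

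**2. How many reach T+100.** The article gives no session lengths. Assume exponential durations with mean m, so the share still playing at 100 min is exp(−100/m):

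- m = 45: exp(−2.22) = 0.108; × 80 = 8.7 people
- m = 60: exp(−1.67) = 0.189; × 80 = 15.1 people
- m = 90: exp(−1.11) = 0.329; × 80 = 26.3 people

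If only those still playing were analysed, and the share were equal in both arms, power for g = 0.58 / 0.62 would be:

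| Share kept | Per arm | Power |
|---|---|---|
| 100% | 40 | 72.6% / 78.2% |
| 75% | 30 | 59.8% / 65.6% |
| 50% | 20 | 43.2% / 48.1% |
| 25% | 10 | 23.3% / 25.9% |

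**3. What each handling does to a rate.** Take someone who plays at a constant rate r and stops at T+35.

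- *Complete cases* (classical repeated measures ANCOVA needs a value at every level): the person is dropped, and so is everyone who stops before the last clock time.
- *Available records* (mixed or long-format fit): the person counts early, but the T+40 and later contrasts still rest on those who continue.
- *Zero after stopping*: interval speed becomes 0 from then on, so the mean largely reflects the share who have stopped.
- *Division by elapsed clock time*: at T+70 the value is 35r/70 = 0.50r and at T+100 it is 35r/100 = 0.35r, although speed while playing never changed. At a clock time t common to everyone, outcome 11 is outcome 10 divided by t and outcome 12 is outcome 1 divided by t. The group comparison then repeats that of the totals.

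For outcomes 1 and 10 the difficulty disappears if totals are held after stopping. Nothing is inserted or bet afterwards, so the final total is the true value at every later clock time.

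**4. Direction of a selection bias (simulation; every input assumed).** Session length is exponential with median 45, 60 or 90 min. Heavier gamblers bet faster and stay longer (log-hazard slope −0.5 per SD). Messages have no effect on betting rate, but after T+10 they raise the stopping hazard, either by 1.5 for all or by 2.0 for lighter and 1.2 for heavier gamblers.

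- Still playing at T+100: 14–33% with messages, 23–46% in control.
- Among these, the messages arm is heavier by 0.12–0.18 SD (common hazard ratio) or 0.28–0.31 SD (differential).
- Mean cumulative amount at T+100 among those still playing: 6–14% higher with messages.
- The same quantity with everyone kept and totals held: 9–15% lower with messages.
- Among those still in play at T+10, the arms differ by less than 0.01 SD.
- If messages do not affect stopping, or stopping is unrelated to intensity, the ratio among those still playing is 0.997–1.007, so there is no material bias.

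**The case against.** **A reader might infer that Model 2 analyses only long players.** The article does not say so. It states no exclusion, listwise deletion or completer set. It adjusts for a time-varying covariate, which suggests a long-format fit using each person's available records. This stands, and the coding of values after stopping may be set out in an analysis plan not shown. It does not remove the point, because available records still leave late rate contrasts on those who continue.

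**Totals and the main question are covered.** This also stands. Outcomes 1 and 10 remain defined after stopping. Model 1 compares money inserted and session duration at each participant's own session end. It does not cover outcomes 10–13.

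**A reader might infer that averaging over six levels, two of them before any message effect, shrinks the effect to 4/6.** The article does not settle this. Table 3 lists six times, but Statistical Methods ties Model 2 to the message times, and the article allows up to four messages. T+0 and session end may not be levels. Dilution would also touch only a time-averaged effect, not time-specific contrasts.

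**The bias may be small relative to noise.** In a harsher assumed scenario, with the stopping hazard doubled, 25% of controls and 11% of the experimental arm remain at T+100, and the spurious speed difference is 0.18 SD. With about 40 × 0.25 = 10 and 40 × 0.108 = 4.3 people, the standard error is √(1/10 + 1/4.3) ≈ 0.58 SD, so the bias is about a third of it. That is fair, but it also shows how little the late contrasts could tell anyone.

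**A reader might also infer that ANCOVA of duration capped at 2 h is wrong.** It is not. Outcome 3 is openly defined with the cap, and capped duration is a legitimate randomised comparison.

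**A single rate after T+10 still has a denominator set by stopping.** This is true. Someone leaving 30 seconds after T+10 contributes 30 seconds, 15 of them behind the message.

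**Conclusion.** The concern holds in a limited form. Model 2 sets fixed clock times for a behaviour that participants may end at any moment, and ending it sooner is a hoped-for effect. For rates 11–13 none of the obvious codings gives a clean randomised comparison at T+40, T+70 or T+100. Each either selects on a post-randomisation event or turns the rate into stopping time or total bets. For outcomes 1 and 10 it is a coding rule that needs fixing.

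The size cannot be computed from the article. The 11%, 19% and 33% reaching T+100 rest on assumed exponential durations. The reversal of sign needs both that messages change stopping and that stopping is related to intensity; without either, the bias is about zero. The documents do not support saying that Model 2 is restricted to long players, or that the trial's comparisons of money and duration at session end are compromised.

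**What to change.** Before the analysis is run, amend Model 2 as follows.

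1. **Outcomes 1 and 10:** carry each participant's final total forward to all later clock times and keep everyone randomised.
2. **Baseline:** treat the T+10 value, measured before any message can act, as a covariate and not as an outcome level. Drop T+0, where counts are zero and rates are undefined.
3. **Outcomes 11–13:** make the main comparison one rate per person from T+10 to that person's own stop, among those whose session has not ended at T+10, adjusted for the 0–10 min rate. This set is fixed before any message. Report later interval rates descriptively, labelled as conditional on still playing. Interpret the main rate alongside session duration, because its denominator depends on stopping.

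A time-to-event analysis of duration, censored at T+02:00:00, is an optional sensitivity analysis and not a correction.

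The cost is plan wording and modest programming. No new data are needed: recruitment has closed, and the article says that no results are available. The price is fewer time-specific contrasts and imprecise rates for people who stop soon after T+10.
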